## Abstract

**Background:**

Acute and chronic pancreatitis constitute a continuum of inflammatory disease of the pancreas with an increasing incidence in most high-income countries. A subset of patients with a history of pancreatitis suffer from recurrence of acute pancreatitis attacks, which accelerate disease progression towards end-stage chronic pancreatitis with loss of exocrine and endocrine function. There is currently no available prophylactic treatment for recurrent acute pancreatitis apart from removing risk factors, which is not always possible. Pain is the primary symptom of acute pancreatitis, which induces the endogenous release of opioids. This may further be potentiated by opioid administration for pain management. Increased exposure to opioids leads to potentially harmful effects on the gastrointestinal tract, including, e.g. increased sphincter tones and decreased fluid secretion, which may impair pancreatic ductal clearance and elevate the risk for new pancreatitis attacks and accelerate disease progression. Peripherally acting µ-opioid receptor antagonists (PAMORAs) have been developed to counteract the adverse effects of opioids on the gastrointestinal tract. We hypothesize that the PAMORA naldemedine will reduce the risk of new pancreatitis attacks in patients with recurrent acute pancreatitis and hence decelerate disease progression.

**Methods:**

The study is a double-blind, randomized controlled trial with allocation of patients to either 0.2 mg naldemedine daily or matching placebo for 12 months. A total of 120 outpatients will be enrolled from five specialist centres in Denmark and Sweden. The main inclusion criteria is a history of recurrent acute pancreatitis (minimum of two confirmed pancreatitis attacks). The primary endpoint is time to acute pancreatitis recurrence after randomization. Secondary outcomes include changes in quality of life, gastrointestinal symptom scores, new-onset diabetes, exocrine pancreatic insufficiency, disease severity, health care utilization, adherence to treatment, and frequency of adverse events. Exploratory outcomes are included for mechanistic linkage and include the progression of chronic pancreatitis-related findings on magnetic resonance imaging (MRI) and changes in circulating blood markers of inflammation and fibrosis.

**Discussion:**

This study investigates if naldemedine can change the natural course of pancreatitis in patients with recurrent acute pancreatitis and improve patient outcomes.

**Trial registration:**

EudraCT no. 2021–000069-34. ClinicalTrials.gov NCT04966559. Registered on July 8, 2021.

## Administrative information

Note: the numbers in curly brackets in this protocol refer to SPIRIT checklist item numbers. The order of the items has been modified to group similar items (see http://www.equator-network.org/reporting-guidelines/spirit-2013-statement-defining-standard-protocol-items-for-clinical-trials/).

## Introduction

### Background and rationale {6a}

Acute and chronic pancreatitis constitute a continuum of fibro-inflammatory disease processes of the pancreas. Patients are often characterized by one or more predisposing risk factors (e.g. smoking, excessive alcohol consumption, gallstones, and genetic predisposition) [1]. If the predisposing risk factors are not modified or removed, there is a high risk of disease recurrence with ensuing tissue damage and disease progression towards end-stage chronic pancreatitis. Hence, approximately 10% of patients who have had a single attack of acute pancreatitis will progress to chronic pancreatitis, while the progression rate increases to 20–30% in patients with recurrent acute pancreatitis [2]. Especially in patients with alcoholic pathophysiology in their first-time acute pancreatitis attack, the progression rate increases significantly compared to other aetiologies [3].

In many cases, recurrent pancreatitis can be related to continuing toxic exposure to smoking and alcohol or unrecognized or inadequately treated biliary stones [4]. However, in 10–15% of cases, the aetiology remains unexplained despite a thorough diagnostic workup [5]. Currently, no prophylactic treatment is available for these patients, who have a high risk of recurrent episodes of pancreatitis. Also, many patients with chronic pancreatitis experience acute flares of pancreatic inflammation (i.e. acute pancreatitis) typically characterized by pain exacerbation that is often managed by opioid prescription. This condition has been termed acute on chronic pancreatitis and contributes to reduced quality of life, increased hospitalization rates, and missed workdays [6]. The current consensus definition of recurrent acute pancreatitis is two or more acute pancreatitis episodes with a complete resolution between the attacks [5]. In the present study, we use the term recurrent acute pancreatitis to include recurring flares of confirmed pancreatitis in patients at various stages on the pancreatitis continuum, which is in line with other ongoing studies [7, 8].

Pain is the cardinal symptom of acute pancreatitis and mediates the release of endogenous opioids, which are further potentiated by exogenously administered opioids used for pain management. Importantly, a large proportion of patients with recurrent and chronic pancreatitis also suffer from abdominal pain between flares of pancreatitis and may be exposed to extended periods of opioid treatment [1]. Opioid exposure is associated with several harmful effects on the gastrointestinal organs that may worsen the disease course of pancreatitis [9]. Most importantly, opioids directly affect the pancreas where they decrease fluid secretion from ductal cells and increase the tonus of the sphincter of Oddi, which in combination may lead to impaired pancreatic ductal clearance of activated pancreatic enzymes and other harmful substances [10]. This promotes intrapancreatic activation of trypsinogen and may initiate a new inflammatory attack (i.e. recurrent pancreatitis) [11]. Exogenously administered opioids have also been shown to have an immunosuppressive effect on both the innate and adaptive immune systems in animal studies. However, these effects have not been sufficiently investigated in human studies [12]. Additionally, increased levels of endogenous and exogenous opioids potentially decrease small intestine motility, which increases the risk of small intestine bacterial overgrowth and impaired intestinal integrity [13, 14]. Together these adverse effects can lead to the translocation of bacteria to the systemic circulation and further potentiate the severity of pancreatitis [15]. Finally, opioid exposure is associated with an excess risk of constipation [13]. In severe cases, this may lead to worsening of abdominal pain and hospitalization due to suspicion of a new pancreatitis attack. Altogether, opioids have several harmful effects on the pancreatic gland and gastrointestinal tract and thus may impact the clinical course of recurrent pancreatitis.

Peripherally acting µ-opioid receptor antagonists (PAMORAs) have been developed to treat opioid-induced bowel dysfunction [16]. As outlined above, the tone in the sphincter of Oddi and pancreatic secretion is partly controlled by endogenous opioids, and during pain attacks, these are upregulated. Therefore, treatment with PAMORAs may counteract the abovementioned adverse effects of endogenous opioids on the pancreatic gland and gastrointestinal tract. This effect may be even more pronounced if exogenous opioids are used in pain management. PAMORAs have, however, never been investigated for this indication. Potentially, the administration of PAMORAs in patients with recurrent pancreatitis is expected to increase pancreatic duct flow [13] and facilitate the clearance of putative pathogenic substances, including intrapancreatic prematurely activated trypsinogen. They may also antagonize the potentially harmful effects of opioids on intestinal integrity and the immune system. The harmful effects of opioids on the pancreatic gland and gastrointestinal organs are illustrated in Fig. 1, along with the treatment targets of PAMORA in relation to recurrent acute pancreatitis.

**Fig. 1 Fig1:**
[figure not shown]
Summary of the harmful effects of endo- and exogenous opioids on the pancreatic gland and gastrointestinal tract in patients with recurrent pancreatitis. Primary and secondary treatment targets for PAMORA are illustrated. *Opioid represented as a morphine molecule

### Objectives {7}

The primary objective of this trial is to investigate if a daily oral administration of the PAMORA naldemedine as compared to placebo will reduce the risk of acute pancreatitis attacks over a 12-month period in patients with recurrent acute pancreatitis.

Secondary objectives are to compare the following parameters between naldemedine and placebo-treated groups over 12 months:Frequency and severity of pain attacksPatient-reported treatment efficacyQuality of lifeGastrointestinal symptoms and bowel functionThe proportion of patients with new-onset diabetes and new-onset exocrine pancreatic insufficiency along with the progression of known pancreatic insufficiency measured as changes in the use of relevant medicationHealth care resource utilizationAdherence to treatment and frequency of adverse events

Exploratory objectives are to compare the following parameters between the treatment groups after 12 months:Ductal and parenchymal pancreatic morphology evaluated by MRICirculating blood markers of fibrosis and inflammation

### Trial design {8}

The study is a multicentre investigator-initiated, double-blind, placebo-controlled, parallel-group study of fixed-dose naldemedine. A group of 120 patients with recurrent acute pancreatitis will be prospectively included from outpatient clinics and randomized to receive oral naldemedine or matching placebo in a 1:1 ratio.

### Methods: participants, interventions, and outcomes

#### Study setting {9}

The study will be conducted at four referral centres for pancreatitis in Denmark and one in Sweden, located at Aalborg, Odense, Copenhagen (Bispebjerg and Hvidovre), and Stockholm. These centres have comprehensive experience in the management of patients with pancreatic diseases. Patients with recurrent acute pancreatitis will primarily be identified and included via the outpatient clinics at the abovementioned institutions. However, they may also be identified during hospital admission if the eligibility criteria are matched.

### Eligibility criteria {10}

#### Inclusion criteria

Signed informed consent before any study-specific proceduresAble to read and understand Danish or Swedish (depending on the study site)Adults aged 18 to 74 years (both inclusive)A diagnosis of recurrent acute pancreatitis with at least one attack of acute pancreatitis within the last 12 months and at least two attacks within 5 years (confirmed as defined by the revised Atlanta Criteria [17])Clinically stable at the time of inclusion defined by no objective, radiological or biochemical signs of acute pancreatitis or other diseases that require hospitalizationThe researcher finds that the participant understands what the study entails, is capable of following instructions, can attend when needed, and is expected to complete the studyThe investigator will ensure that fertile female participants have a negative pregnancy test before treatment initiation and use contraception during the study period. The following methods of contraception, if properly used, are generally considered reliable: oral contraceptives, patch contraceptives, injection contraceptives, vaginal contraceptive ring, intrauterine device, surgical sterilization (bilateral tubal ligation), vasectomized partner, double barrier (condom and pessary), or sexual abstinence. Methods of contraception will be documented in the source documents

#### Exclusion criteria

Known hypersensitivity towards study medicationPatients with known or suspected gastrointestinal obstruction or perforation or patients at increased risk of recurrent obstruction due to the potential for gastrointestinal perforation (e.g. peptic ulcer disease, acute colonic pseudo-obstruction, malignancy of the GI tract, Crohn’s disease)Previous pancreatic surgery including pancreaticoduodenectomy or other procedures involving the pancreatic head and sphincter of OddiKnown severe renal insufficiency (defined as estimated glomerular filtration rate < 30 ml/min)Female participants that are lactatingPre-existing severe comorbidities (evaluated by the investigator prior to inclusion)Attack of acute pancreatitis requiring admission within 4 weeks prior to inclusionGallstone aetiology of recurrent acute pancreatitis (magnetic resonance cholangiopancreatography or endoscopic ultrasound excluding biliary stones must be available prior to enrolment)Treatment with strong CYP3A4-inhibitors (itraconazole, ketoconazole, ritonavir, indinavir, saquinavir, telithromycin, grapefruit juice and clarithromycin), strong CYP3A inducers (e.g. St. John’s wort (Hypericum perforatum), rifampicin, carbamazepine, phenobarbital and phenytoin) or P-glycoprotein inhibitors (e.g. cyclosporine).

#### Who will take informed consent? {26a}

Medical doctors affiliated with the study or trained site staff with relevant knowledge of the disease and conducting clinical trials will give the potential participants information regarding the study. The participant will be informed thoroughly about the purpose of the study, the specific procedures the study entails, and potential benefits and risks. All patients will be informed orally and written before deciding whether they want to participate in the study. Furthermore, they will be informed that they can withdraw from the study at any given time without giving a reason. The interview will take place at the respective inclusion sites at the outpatient clinic.

#### Additional consent provisions for collection and use of participant data and biological specimens {26b}

When the participant signs the informed consent form, they will be asked to fill in a separate consent form if they are willing to contribute their blood samples to a biobank.

### Interventions

#### Explanation for the choice of comparators {6b}

Since there is no established preventive treatment for recurrent acute pancreatitis, the comparator is a matched placebo tablet with an identical appearance to the active tablets but without the active component naldemedine.

#### Intervention description {11a}

Patients with recurrent acute pancreatitis will receive oral treatment with naldemedine 0.2 mg daily (standard clinical dose) or matched placebo tablets once daily. Naldemedine and placebo will be presented as identical tablets, taken with approximately 100 ml water. Since the aim is to evaluate the long-term effects of PAMORAs on the frequency of pancreatitis attacks and disease progression, a long treatment period of 12 months has been chosen.

#### Criteria for discontinuing or modifying allocated interventions {11b}

If a patient experiences intolerable side effects when taking 0.2 mg naldemedine or placebo daily, a single downward dose titration to one tablet every other day is allowed, with this dose being the final dosage for the remainder of the study. Typical side effects associated with naldemedine are diarrhoea, abdominal pain, and other mild gastrointestinal symptoms. These treatment-related symptoms are not associated with a higher discontinuation rate than placebo [16].

A participant should be withdrawn from trial, if at any time:It is the wish of the participant for any reasonThe investigator judges it necessary due to medical reasonsThe investigator judges severe non-compliance to protocolThey experience intolerable side effects despite tapering the dose of naldemedine to 0.2 mg (or matching placebo) every other day

#### Strategies to improve adherence to interventions {11c}

A detailed count of the study medication dispersion and return will be kept for all participants. Patients will be asked to fill out a study drug diary to document adherence. Furthermore, patients will be followed by monthly telephone consultations with the study personnel during the entire study period.

#### Relevant concomitant care permitted or prohibited during the trial {11d}

Patients with recurrent acute pancreatitis included in the study will continue their scheduled visits and examinations in the outpatient clinic while participating in the study. Patients will also receive routine treatment deemed necessary by the responsible physician according to the usual standard of care and clinical guidelines. All medications are registered in the patient’s case report form (CRF) at baseline, including name, strength, frequency of dosing, and reason for use. In case of a change in medication during the trial period (dose change or discontinuation), this will be documented in the CRF. Patients will be asked to phone the study centre at any time if they need to speak to study personnel, should they require additional concomitant medication.

#### Provisions for post-trial care {30}

When patients reach the end of the study or discontinue treatment for other reasons, they will all revert to their routine visits and examinations at their respective tertiary outpatient clinics.

All participants with unresolved events (adverse event (AE) and serious adverse event) at the end of the study, except those who dropped out before randomization or starting active treatment, must be included in safety follow-up visits until the symptoms resolve or are deemed stable by the treatment-responsible doctor.

All participants will be covered by the patient insurance of the respective site of trial conduction. Participants are advised to seek consultancy from their insurance company if they plan to travel during or right after participation in the study, as participation in a trial involving medical treatment may alter private insurance status.

### Outcomes {12}

#### Primary outcome

The primary outcome is time to recurrence of acute pancreatitis verified by the revised Atlanta Criteria. This outcome is compared between the group receiving naldemedine and the placebo group during the 12-month treatment period.

The revised Atlanta Criteria is the current gold standard for the diagnosis of acute pancreatitis, and it requires a minimum of two out of three of the following features:(i)Abdominal pain typical for acute pancreatic (acute onset of a persistent, severe, epigastric pain often radiating to the back)(ii)Serum lipase or amylase levels at least three times greater than the upper limit of normal(iii)Characteristic findings of pancreatic inflammation on contrast-enhanced computed tomography, MRI, or transabdominal ultrasonography [17]

#### Secondary outcomes

Difference between treatment groups in disease severity assessed by the Atlanta CriteriaThe difference between treatment groups in frequency and severity of pain attacks (without fulfilling acute pancreatitis criteria), assessed by questionnaires and monthly interviews after the 12-month periodDifference in patient’s global impression of change between treatment groups assessed by a questionnaire at 12 months follow-upChanges in quality of life between treatment groups from baseline to 12 months follow-up assessed by a questionnaireChanges in gastrointestinal symptoms and bowel function between treatment groups from baseline to 12 months follow-up assessed by questionnairesProportion of patients with new-onset diabetes according to the WHO criteria [18] and changes in endocrine pancreas function between treatment groups from baseline to 12 months follow-up assessed by haemoglobin A1c (HbA1c)Proportion of newly diagnosed exocrine pancreatic insufficiency defined by the use of pancreatic enzyme replacement therapy or changes in exocrine pancreas function between treatment groups from baseline to 12 months follow-up assessed by a faecal-elastase testDifference between treatment groups in health care resource utilization (measured in frequency and type of health services used, e.g. admission rate and duration) during the 12-months treatment periodDifference between treatment groups in adherence to treatment and frequency of adverse events during the 12-months treatment period assessed by study drug diary, return of unused medicine, and regular interviews

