**Table 1 Tab1:**
[figure not shown]
Schedule for enrolment, interventions, and assessments including visits for patients

^**a**^Baseline variables: sex; age; the number of recurrences of acute pancreatitis before inclusion, presence of chronic pancreatitis and aetiology of pancreatitis; use of opioids, weak analgesics, and other medication; alcohol consumption and smoking status; Information regarding diabetes mellitus and use of pancreatic enzyme replacement therapy; Previous invasive treatment for pancreatitis; Comorbidities based on the Charlson Comorbidity Index [19]

^**b**^Verified recurrence(s) and severity of acute pancreatitis based on the Atlanta Criteria and pain attacks not fulfilling the Atlanta Criteria; Pain attack diary and the modified Brief Pain Inventory Short Form are filled in once for each attack

^**c**^Patient Global Impression of Change questionnaire and European Organization for Research and Treatment of Cancer Quality of Life questionnaire (EORTC QLQ-C30); Gastrointestinal Symptom Rating Scale and Bristol Stool Form Scale

^**d**^Study drug diary and adverse events diary

*Magnetic resonance imaging

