#### Sample size {14}

The sample size calculation is based on the following assumptions:Included recurrent acute pancreatitis patients will have one pancreatitis attack at least once pr. yearNaldemedine is expected to reduce the pancreatitis attack rate by 50%Power is set to 90% at a 2-sided alpha level of 0.05

These assumptions analysed by the extended (recurrent) Cox model yield a required sample size of 120 patients observed for 12 months. We implement a planned interim analysis after 60 participants have been enrolled to allow re-estimation of sample size requirements and to examine adverse event rates.

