## Data collection and management

### Plans for assessment and collection of outcomes {18a}

#### Clinical outcome and health resource utilization

The clinical outcomes will be documented through questionnaires and a pain attack diary, filled in before, during, and after treatment. Participants will be asked to fill in the pain attack diary, and the modified Brief Pain Inventory Short Form for each pancreatitis attack during the study period. Hospital admissions and whether patients fulfilled the Atlanta criteria for acute pancreatitis during admission will subsequently be documented using the medical files along with the severity of the attack. To assess the effects of the treatment on quality of life, patients will also be asked to fill in the following: (i) the European Organization for Research and Treatment of Cancer Quality of Life Questionnaire (EORTC QLQ-C30) and (ii) the Patient Global Impression of Change Questionnaire. For a detailed description of these questionnaires, see the section below. The patients’ medical files at 12 months follow-up are used to document health resource utilization, readmission rate, and total length of hospital stays during the recovery phase of pancreatitis.

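### Atlanta severity is recorded only for attacks, which the drug is meant to prevent, and the severity outcome sets no value for attack-free patients; define it over all randomised patients.

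*Protocol article*

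**What the plan says.** In the protocol article, the list under Secondary outcomes opens with "Difference between treatment groups in disease severity assessed by the Atlanta" Criteria. It gives no summary measure, population or period for this outcome.

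Two other places show what severity refers to:
- Table 1, note b, schedules "Verified recurrence(s) and severity of acute pancreatitis based on the Atlanta Criteria".
- Clinical outcome and health resource utilization says that the question of who "fulfilled the Atlanta criteria for acute pancreatitis during admission will subsequently be documented using the medical files along with the severity of the attack".

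In both, severity is a property of a verified attack. Under Objectives, the trial asks whether naldemedine "will reduce the risk of acute pancreatitis attacks over a 12-month period", and the Sample size section expects the attack rate to fall by half.

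The section on statistical methods for primary and secondary outcomes applies intention to treat to all analyses and names regression and logistic models for secondary endpoints. The section on non-adherence and missing data names last observation carried forward.

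**The concern.** Treatment is expected to decide who has a severity value at all. A comparison among patients with an attack then sets two groups side by side that were formed after randomisation, by an event the drug affects. They need not be alike even though the arms were.

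If the drug removed mainly mild attacks, the attacks that remain would be more severe on average. The first-listed secondary outcome could then appear to contradict a real benefit. If it removed mainly severe attacks, the remaining ones would look milder, but the size of the gain would still be misjudged. The Background links opioid effects to the severity of pancreatitis, so a severity result is likely to be read as evidence on mechanism or safety.

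**Working it through.** **Inputs**
- Placebo rate: 1 attack per patient-year (Sample size; worded there as a minimum, used here as the mean).
- Rate ratio: 0.5 (Sample size).
- Error rates: "Power is set to 90% at a 2-sided alpha level of 0.05".
- Size and follow-up: "required sample size of 120 patients observed for 12 months".
- Allocation: patients are "randomized to receive oral naldemedine or matching placebo in a 1:1 ratio", so 60 per arm.
- Assumptions: Poisson attacks and complete follow-up.
- The article gives neither the Atlanta grades nor their frequencies. 'More severe' below means moderately severe or severe. Its share is assumed to be 20%, with a range.

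**1. The plan's own figure.** Schoenfeld events = 4 × (1.960 + 1.282)² / (ln 0.5)² = 87.5, so 88. Expected events per patient = (1.0 + 0.5)/2 = 0.75. N = 88/0.75 = 117.3, so 118, within 3% of 120. With 120 patients there are 90 expected events and 90.8% power. The rates are thus read as the plan uses them.

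**2. Who has a severity value.** Probability of at least one attack = 1 − e^(−rate).
- Placebo: 1 − e^(−1) = 0.632; × 60 = 37.9 patients.
- Naldemedine: 1 − e^(−0.5) = 0.393; × 60 = 23.6 patients.
- No value: 22.1 + 36.4 = about 58 of 120.

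**3. Only mild attacks prevented, share set per patient.** If 20% of placebo patients with an attack have a more severe one, that is 0.20 × 37.9 = 7.6 patients. The drug leaves these attacks untouched, so naldemedine also has 7.6.
- Among patients with an attack: 7.6/37.9 = 20% versus 7.6/23.6 = 32%. OR = (0.321/0.679)/(0.20/0.80) = 1.9.
- Among all randomised patients: 7.6/60 in each arm.
- At a share of 10% the OR is 1.7; at 30% it is 2.2.

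**4. Only mild attacks prevented, share set per attack.** With 20% of placebo attacks more severe, the rate of such attacks is 0.2 per patient-year in both arms.
- All randomised: 1 − e^(−0.2) = 18.1% in each arm.
- Patients with an attack: 0.181/0.632 = 28.7% versus 0.181/0.393 = 46.1%, OR 2.1.
- In 20,000 simulated trials, a two-sided 5% test of proportions among patients with an attack was significant towards harm in 29%. Over shares of 10% to 40% the OR runs from 1.8 to 4.7 and false harm from 16% to 74%.
- The same test in all randomised patients gave about 2.5%, the nominal level.

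**5. All grades halved equally.** The share of attacks that are more severe is 20% in both arms. The share of attack patients with at least one more severe attack is 28.7% versus 24.2% (1 − e^(−0.1) = 9.5%; 0.095/0.393), so no false harm. Per randomised patient it is 18.1% versus 9.5%, a gain that the per-attack share does not show.

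**6. Severity rising with a patient's underlying attack risk, not changed by the drug.** With gamma frailty of variance 0.5 to 2 and shares of 10% to 30% (8,000 trials per setting), patients with an attack number about 33 versus 22 down to 25 versus 18. False harm is about 3% to 5%, against 2.5% nominal.

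**The case against.** **The population is not stated.** A reader might infer that the plan commits to a non-randomised comparison. It does not say so. The outcome names no population, all analyses are promised by intention to treat, and an all-randomised definition would fit both statements. An analysis plan that is not shown may contain one. This stands as a limit on the claim. It does not remove the point: severity is attached to attacks, and intention to treat cannot be applied until attack-free patients have a value. Last observation carried forward supplies none, since the severity of earlier attacks is not among the baseline variables in Table 1, note a.

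**The false-harm scenario is one-sided.** A reader might infer that spurious harm is the expected result. The documents do not support that. The Background suggests that opioid effects worsen severity and that the drug may counteract them, which points towards fewer severe attacks if anything. Step 5 shows no false harm and step 6 only a little. Even the example in step 3 would not be significant on its expected counts: the pooled proportion is 15.2/61.5 = 0.247, the standard error is √[0.247 × 0.753 × (1/37.9 + 1/23.6)] = 0.113, and z = 0.121/0.113 = 1.07, p about 0.28. This stands too.

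**Pain attacks.** A reader might extend the point to "frequency and severity of pain attacks (without fulfilling acute pancreatitis criteria"). That does not follow. Frequency is defined for every randomised patient, with zero possible. An attack turned from pancreatitis into pain alone is credited in the primary endpoint. Pooling the two kinds of attack is a preference about the endpoint.

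**Conclusion.** The point holds in a limited form. The severity outcome is tied to an event that treatment is meant to halve, and it is not defined for the roughly 58 of 120 patients expected to have no attack (22 on placebo, 36 on naldemedine). Those counts rest on a mean placebo rate of 1, a rate ratio of 0.5 and Poisson attacks; with between-patient variation fewer patients would have a value.

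Whether a comparison among patients with an attack misleads depends on the mix of attacks prevented. It shows 20% versus 32%, with no true difference per randomised patient, if only mild attacks are prevented and the assumed 20% share applies. The distortion is small if only underlying risk differs between patients, and there is no false harm if all grades fall equally. This concerns one secondary outcome. The primary analysis and the sample size of 120 are unaffected.

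**What to change.** Reword the first secondary outcome so that every randomised patient contributes. Either of these would do:
- the rate of moderately severe or severe Atlanta attacks per patient-year, analysed in the recurrent-event model used for the primary endpoint; or
- the worst Atlanta grade over 12 months as an ordinal outcome, with no attack as the lowest category.

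Name the grades counted, and label any comparison of severity per attack as descriptive. Settle the wording before unblinding.

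The cost is one reworded outcome and one model on data already collected. The price is precision. At an assumed 20% share there would be about 60 × 0.2 = 12 more severe placebo attacks. With 12 versus 6, the standard error of the log rate ratio is √(1/12 + 1/6) = 0.5, so a ratio of 0.5 would have a 95% interval of about 0.19 to 1.33 (Poisson). The result should be reported as an estimate with its interval.
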